## Methods/Design

Six K–8 schools in the School District of Philadelphia were randomly assigned to either Consultation or Consultation plus Coaching (See Figure 2). A stratified random assignment list of schools to condition was generated using a computerized random assignment program [77]. Schools were stratified to group one if their baseline School Climate (CREST) scores were below the median CREST scores or to group two if the CREST scores ≥ the median value. The units of analyses for Tier 1 are all of the students in those K-8 schools (650 per school), leadership team members (eight per school) and other school staff (30 per school). The units of analyses for Tier 2 are the children meeting criteria for inclusion in one of the GCBT groups (enroll a total of 367 students assuming a 17% dropout; approximately 51 eligible students per school), the school counselors (two per school) conducting the GCBT groups, and the groups themselves (14 per school; see Table 1).

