### Participants

Tier 1 research activities will include 48 teachers, administrators and parents in the leadership teams, 180 school staff for the assessment of school climate, and approximately 3,900 students. Participants in Tier 2 will be 12 counselors and approximately 306 evaluable children who have, or are at risk for, externalizing or anxiety disorders. School personnel will provide all services. Information pertaining to each school will be considered nested within school ‘cluster’ and will be defined as such in the statistical analyses.

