### Data analytic plan

The statistical analyses for each of the study aims are described below: in addressing aim one, mean fidelity and its 95% confidence intervals for Tier 1 will be calculated using 20 randomly selected participants from each of the six schools during years three, four, and five (120 total per year). The 95% confidence intervals will be presented by C & C + C for all schools combined and for each school. Content and process fidelity data for Tier 2 will be obtained by scoring 14 video recorded sessions per each of the treatment groups. Perception of School Climate (aim two) during year one will be surveyed by a randomly selected sample of teachers, support staff and administrators from each participant school. The randomly selected sample will consist of similar proportion of teachers, support staff and administrators within each school. The questionnaire [101] will be completed at the end of years one, two, three, four, and five. This 31-item, 5-point Likert type scale checklist has four factors. Each factor’s total score will be analyzed separately. School personnel no longer present in the school during subsequent years will be replaced.

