The general analytical approach for testing our hypotheses will be the Laird and Ware mixed effects model [112] and the Generalized Estimating Equation (GEE) approaches [113,114]. Mixed effects and GEE are statistical approaches based on regression techniques for analyzing correlated data collected repeatedly from the same subject. The study design will allow us to examine the between- subjects effect related to the two levels of support, and a within-subjects effect corresponding to time points (five time points), as well as a type of support (C, C + C) by time interaction effect. These analyses will be conducted using SAS Proc Mixed, which utilizes the mixed effects models, and SAS Proc Genmod, which utilizes GEE [115]. Both the mixed effects model and GEE approaches allow estimation of fixed effect parameters such as time, and time by treatment interaction. If the interaction term is significant, it indicates that change in school climate and/or reduction in ODRs over time is significantly different between the two levels of support. If the interaction term is statistically not significant, the changes over time for the two primary outcomes will be presented by the time effect only, which represents both levels of support. The advantage of utilizing these methods is that all information available from each student is used, including variables with missing observations. In the proposed analyses, we will consider students measured within classes are correlated and will be nested within classes. Nested analysis will be chosen as part of Proc Mixed and Proc GEE, as such, the intraclass ‘intracluster’ correlation (ICC) will be part of the overall variance covariance matrix.

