Changes from pre- to post- implementation in diagnostic status, symptom severity and impairment level, coping skills and academic productivity during Implementation across all schools, regardless of level of support, will be analyzed using McNemar tests. For each of the listed primary outcomes, a series of 2X2 tables will be constructed to test changes from pre- to post- in the pertinent categories using McNemar tests. Alpha level will be adjusted to 0.025 based on Bonferroni criteria for multiple comparisons. We will also use McNemar tests to test the hypothesis that the pre- to post- level of improvement in diagnostic status, symptom severity, impairment level, coping, and academic productivity obtained during Implementation will be maintained during Sustainability among schools receiving C + C.

We would like to determine whether pre- to post- improvement in diagnostic status, symptom severity, impairment level, and academic productivity differ by support condition during the implementation phase. In addressing this research question, and for the sake of simplifying the statistical analysis, each student will be categorized as either improved or not improved based on change from pre- to post-. A category one will be assigned if a student’s diagnostic status, for example, changes either from positive to intermediate, intermediate to negative, or positive to negative. Otherwise a score of zero will be assigned. Similar coding will be used for symptom severity, coping, impairment level, and academic productivity. We will use chi-squared tests to compare the proportion of (yes/no) for each of the primary outcomes between C and C + C type of supports. To examine changes in the rate of ODRs between baseline and follow up during each school year, the number of students with at least one ODR will be defined at baseline and at the follow up and a 95% confidence interval for such changes will be constructed for each of the five years.

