### Challenges and limitations

Implementing SWPBIS with mental health supports in under-resourced urban schools presents a number of challenges. In our pilot study where we developed and piloted the interventions, we faced repeated leadership changes at the district level, staff turnover at the school level, and limited parent participation [74]. However, we also found strong and consistent support among second-level administrators (*e.g.*, regional superintendents) at the District level and committed leadership teams that were able to recruit new members who functioned effectively. With the lessons learned from our pilot study, we are able to more effectively support the schools in successfully implementing SWPBIS while receiving either level of support. We have redoubled our efforts at helping schools to increase parental collaboration and support, which lead to more parent participation. We have also designed the implementation strategy to fully utilize existing policy and infrastructure (*e.g.*, implementation of District-wide practices to promote students’ success; utilizing school counselors and school facilities for Tier 2 interventions) to limit strain on resources so that the proposed program will be sustainable.

A limitation is that we are conducting the study in six schools within a single school district (though it is one of the largest and most diverse school districts in the country), which limits generalizability to schools in different parts of the country. Including a relatively small number of schools limits our ability to examine the clustering effect of school classes and schools. In this study, the unit of randomization is the school but the unit of analysis (aim two) is the student. A cluster randomized approach would have been an appropriate design if a much larger number of schools were included in the study. However, it is anticipated that the degree of similarity in treatment response among students within a class will be poorly correlated, and therefore the intraclass correlation coefficient within clusters will be small and its effect on the overall variance between schools would be minimal. However, an appropriate cluster analyses will be conducted using nested analysis. The NESTED Procedure of SAS [115] is an example of such analysis. We expect that our findings will inform implementation research in schools and procedures to be incorporated into larger-scale trials in urban schools in the future.

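### Schools were randomised, but the C versus C + C child-outcome tests are chi-squared tests on individual students, with true type I error up to about 30% at the protocol's own 5% ceiling for school variance

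*Protocol article*

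**What the plan says.** Under Methods/Design, "Six K–8 schools in the School District of Philadelphia were randomly assigned to either Consultation or Consultation plus Coaching". The number per arm is not given in words. Table 1 implies three: 1,950 Tier 1 students per arm at 650 per school, and 153 Tier 2 students per arm at about 51 per school.

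Under Data analytic plan, the between-arm comparison of child outcomes is reduced to a binary variable to keep the analysis simple: "each student will be categorized as either improved or not improved based on change from pre- to post". The test is then named: the investigators will "use chi-squared tests to compare the proportion of (yes/no) for each of the primary outcomes between C and C + C". No school term or adjustment is mentioned there.

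Three other places bear on clustering:

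- Participants: "Information pertaining to each school will be considered nested within school", with school to be defined as the cluster in the analyses.
- Data analytic plan, in the paragraph on mixed models and generalised estimating equations: "we will consider students measured within classes are correlated and will be nested within classes". The level named is class.
- Challenges and limitations: the protocol concedes that "the unit of randomization is the school but the unit of analysis (aim two) is the student". It expects little within-class correlation and then promises a nested cluster analysis, with a SAS procedure as an example.

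Sample size justification and statistical power takes changes in diagnostic status to be independent within schools, because school explained less than 5% of variance in an evaluation of one of the two group programmes.

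**The concern.** When whole schools are allocated, an ordinary chi-squared test on children counts any school-to-school difference in improvement rates as evidence about coaching. With three schools per arm, a modest difference between schools can pass for an arm effect.

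This is the trial's only randomised contrast, and it covers diagnostic status, which the sample-size section names as the primary outcome. Errors would also travel further. Aim four builds additional cost-effectiveness ratios for outcomes on which the comparison is significant, so a false positive would feed into the cost advice given to school districts.

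The statements about clustering do not settle which analysis applies. An analyst who follows the named test and one who follows the Participants section would report different p-values from the same data.

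**Working it through.** **The plan's own figure.** No power or error rate is stated for the between-arm tests. The only power figure is 92% for the pre/post McNemar test (300 students, two-sided alpha 0.01, discordant cells 0.425 and 0.175). With d = 0.25 and s = 0.60, power = Φ[(√n·d − 2.576·√s)/√(s − d²)]. For n = 300 this is Φ[(4.330 − 1.995)/0.733] = 99.9%. For n = 150 it is Φ[(3.062 − 1.995)/0.733] = 92.7%. The stated figure is therefore not reproduced at 300. That is a separate matter, and it says nothing about the comparison of C with C + C.

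**Inputs.**
- 51 children per school (Methods/Design) and 153 per arm (Table 1).
- Three schools per arm, inferred from Table 1.
- School share of variance (ICC) below 0.05 (sample-size section). This is the only such figure. ICC values of 0.01 and 0.02 are assumptions within that range.
- Alpha: none is stated for the chi-squared tests. The McNemar paragraph gives 0.025. Results are shown for 0.05 and 0.025.
- Improvement rate near 50% for the detectable differences (assumption).

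**Type I error of the student-level test.** Design effect DE = 1 + (51 − 1) × ICC. True two-sided error = 2 × [1 − Φ(z/√DE)], with z = 1.96 for nominal 0.05. At ICC 0.05, DE = 1 + 50 × 0.05 = 3.5, 1.96/√3.5 = 1.048, and the error is 0.295.

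**Detectable difference, 80% power, alpha 0.05.** For the naive test: (1.960 + 0.842) × √(2 × 0.25/153) = 16.0 points. For a t-test on six school proportions with 4 degrees of freedom, the required noncentrality is 3.761, so the difference is 3.761 × √(0.5 × DE/153).

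| ICC | DE | Effective children per arm (153/DE) | True error, nominal 5% | True error, nominal 2.5% | Detectable difference, school t-test |
|---|---|---|---|---|---|
| 0 | 1.0 | 153 | 5.0% | 2.5% | 21.5 points |
| 0.01 | 1.5 | 102 | 11.0% | 6.7% | 26.3 points |
| 0.02 | 2.0 | 76.5 | 16.6% | 11.3% | 30.4 points |
| 0.05 | 3.5 | 43.7 | 29.5% | 23.1% | 40.2 points |

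At nominal 5%, the error doubles at an ICC of about 0.008 and triples at about 0.017.

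**Simulation check.** Beta-binomial data for three versus three schools of 51, with improvement rates of 0.3 to 0.6, gave chi-squared error at nominal 5% of 10% to 11% at ICC 0.01, 16% to 17% at 0.02 and 29% to 30% at 0.05. The t-test on school proportions stayed between 0.047 and 0.052 for ICC 0 to 0.05.

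**The case against.** The strongest reply is that the protocol does not ignore clustering. It names mixed models and generalised estimating equations as its general approach, says school will be the cluster, admits the mismatch of units as a limitation and promises a nested analysis. Nesting in classes and nesting in schools are compatible, and a full list of random effects may sit in a document not shown here.

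For Tier 1 this reply largely stands. Naming class does not exclude school, so the fair request is to state both levels. For the child-outcome tests it does not stand. There the article names a specific test with no cluster term, and nothing says that the promised nested analysis replaces or adjusts it. The expectation of weak correlation within classes also concerns a level below the one randomised.

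A second reply is that the ICC may be small. That is fair as to size: the error is 8.0% at an ICC of 0.005. It does not rescue the independence assumption, because a share below 5% still allows a design effect of up to 3.5 with 51 children per school.

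Several stronger readings are tempting, but the documents do not support them:

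- A reader might infer that false-positive risk is several times nominal as a fact. That depends on an ICC for which only a borrowed ceiling is given.
- A reader might apply the same formula to 650 students per school and infer far greater inflation in Tier 1. That assumes school is left out, contrary to Participants. It also uses a cross-sectional ICC for a support-by-time test, in which stable school differences largely cancel. School climate comes from 30 staff per school, not from students.
- A reader might infer that the Tier 1 fidelity intervals are too narrow because each "will be calculated using 20 randomly selected participants from each of the six schools". The protocol gives no ICC for fidelity, names no interval for the arm difference, and also plans to show each school separately.
- A reader might infer that the median split on baseline climate forces unequal strata across arms. Tied scores could give strata of two and four, and no scores are reported.

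**Conclusion.** The defect holds for the named chi-squared tests of C against C + C on Tier 2 child outcomes. They analyse children as independent although schools were randomised, and they conflict with the protocol's own statements that school will be the cluster.

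At nominal 5%, the true type I error is about 11%, 17% and 30% at ICC 0.01, 0.02 and 0.05. The last is about six times nominal, and it is an upper figure under the protocol's ceiling, not an estimate for this trial.

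The result rests on three schools per arm, equal school sizes of 51 and a normal approximation confirmed by simulation. Further clustering by therapy group or counsellor could add to the error, but the documents give no figure for it. No numerical claim is made for Tier 1 or for fidelity.

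**What to change.** Replace the between-arm chi-squared tests with one named school-level analysis, chosen before outcome data are seen:

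- a two-sample t-test on the six school proportions improved, with 4 degrees of freedom; or
- a mixed logistic model with a random school effect and small-sample degrees of freedom of about 4.

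The first is simple, and its error rate was checked above. The error rate of the second with six schools was not checked here and should be simulated before it is adopted. An unstratified three-versus-three permutation test is not a substitute at the 5% level, because its smallest two-sided p-value is 2/20 = 0.10.

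Then reconcile Participants, Data analytic plan, and Challenges and limitations. State that school is a level in the Tier 1 models as well as class, and say which test the nested analysis refers to.

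The change needs revised wording and a little code, but no new data. The real cost is precision: the detectable difference goes from about 16 points under the naive test to about 22 to 40 points for ICC 0 to 0.05. The protocol should therefore describe the between-arm child-outcome comparison as having limited precision, and reports should lead with the estimate and its school-level interval.

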### Screening, demographics, service utilization

Counselors will ask teachers to complete the SDQ, a mental health screening questionnaire [78,90,91], for children who accumulate ≥3 ODRs or who are referred by a subcommittee of the LT charged with monitoring at-risk children. Children who score ≥1 SD [92] on the Conduct Problems or Emotional Symptoms scales will be invited to participate in a thorough diagnostic assessment.

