#### Children’s functioning

We will collect children’s academic performance, absenteeism, and office discipline referrals (ODR) throughout the five years of the project. Absenteeism data will be collected from the school’s daily attendance records. Academic performance will be taken from the state’s mandatory testing for reading and math for all students. ODRs will be collected using a web-based system for monitoring ODRs to assist in intervention planning and evaluation [100]. These data will be used for determining inclusion into Tier 2 and to measure outcomes. We will also record in- and out-of-school suspensions per 100 students per year and percentage of students receiving suspensions. These indices are reliable and valid for measuring intervention effects [82].

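### The yearly ODR analysis is announced as a change in rate but counts students with at least one ODR, and the main ODR model gives no scale

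*Protocol article*

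**What the plan says.** All of this is in the protocol article.

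- **Data analytic plan, purpose of the yearly analysis:** "To examine changes in the rate of ODRs between baseline and follow up during each school year".
- **Same sentence, the variable:** "the number of students with at least one ODR will be defined at baseline and at the follow up".
- **Same sentence, the analysis:** "a 95% confidence interval for such changes will be constructed for each of the five years". It attaches no test and no comparison of the support conditions to this variable.
- **Data analytic plan, mixed-model/GEE paragraph:** a significant support-by-time interaction is read as showing that "change in school climate and/or reduction in ODRs over time is significantly different between the two levels of support". If the interaction is not significant, "the changes over time for the two primary outcomes will be presented by the time effect only". Here ODRs are one of the two primary outcomes, but the text does not say whether the response is a count, a rate or a yes/no variable.
- **Children's functioning:** "ODRs will be collected using a web-based system for monitoring ODRs to assist in intervention planning and evaluation". Collection runs through all five project years, so counts per student should be available.
- **Screening, demographics, service utilization:** teachers complete the screening questionnaire "for children who accumulate ≥3 ODRs or who are referred by a subcommittee of the LT charged with monitoring at-risk children".

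**The concern.** A rate and a prevalence answer different questions. The share of students with any ODR moves only when students cross between none and one. It does not register a fall from eight to one, or a halving among students who are referred again and again.

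Children with three or more ODRs have one of the two routes into Tier 2 screening. A child who enters by that route can improve a great deal and stay in the same category.

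The article keeps the two measures apart elsewhere. For suspensions, Children's functioning records both a rate per 100 students per year and the percentage of students suspended, and the aim three analysis divides the number of suspensions by the number of students. For ODRs the word rate is used, but only the yes/no form is defined.

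At stake is an outcome named in aim two, treated as primary in the mixed-model/GEE paragraph, and used as an effectiveness measure in the cost analysis. The yearly interval could show almost no change in a school year when total referrals fell clearly.

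**Working it through.** **Inputs.** From the article: 650 students in each of six schools, 3,900 in all. The article gives no ODR mean, dispersion, prevalence, effect size or power, so there is no ODR figure to reproduce. Assumed: negative binomial counts with mean m and dispersion k (variance m + m²/k), 3,900 independent students at each time point, two-sided 5% level.

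**Step 1. Uniform 15% fall (m₂ = 0.85m).**

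- Yes/no variable: p = 1 − (1 + m/k)^(−k); z = (p₁ − p₂) / √[(p₁q₁ + p₂q₂)/3,900].
- Count: z = −ln(0.85) / √[(1/m + 1/k + 1/m₂ + 1/k)/3,900].
- Power = Φ(z − 1.96). Relative efficiency of the cut = (z for yes/no ÷ z for count)². Information lost = 1 − efficiency.

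Worked case, m = 1, k = 0.3:

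- p₁ = 1 − 4.333^(−0.3) = 0.356; p₂ = 1 − 3.833^(−0.3) = 0.332. The difference is 0.0241 and its standard error √(0.4510/3,900) = 0.01075, so z = 2.24 and power is 61%.
- Count: 0.1625 / √(8.843/3,900) = 0.1625/0.0476, so z = 3.41 and power is 93%.
- Efficiency (2.24/3.41)² = 0.43, a loss of 57%.

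Range over k = 0.2, 0.3 and 0.6:

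| Mean ODRs per student | Efficiency of the cut | Information lost |
|---|---|---|
| 0.1 | 0.80–0.89 | 11–20% |
| 0.25 | 0.65–0.77 | 23–35% |
| 0.5 | 0.52–0.64 | 36–48% |
| 1 | 0.40–0.49 | 51–60% |
| 2 | 0.31–0.34 | 66–69% |

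At means of 0.5–2, power is 39–85% for the yes/no variable and 76% to over 99% for the count. At a mean of 0.1 the two differ by only about 4 to 7 percentage points.

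**Step 2. Where the loss reaches one half.** A separate calculation used the Fisher information for a log rate ratio, with variance m + a·m² (so a = 1/k). The loss reaches 50% at a mean of about 1.26 for Poisson counts, 1.0 at a = 1, 0.81 at a = 2, 0.58 at a = 4 and 0.37 at a = 8. Over means of 0.1–2 and a from 0 to 8, the loss runs from 5% to about 72%.

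**Step 3. Fall confined to high-rate students.**

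- Underlying rates of 3 or more halved (m = 1, k = 0.3): total ODRs fall 27%, while the share with at least one moves from 35.6% to 34.7%.
- A 40% cut only in students with three or more ODRs, none reaching zero: total ODRs fall 21% (m = 0.5, a = 4), 24% (m = 1, a = 2), 29% (m = 1, a = 4) or 35% (m = 2, a = 4), and the share does not change.
- The same cut made by removing ODRs at random, so that some students reach zero: total ODRs again fall 21–35%, and the share falls by about 1% in relative terms (for example 33.1% to 32.8%).

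**Step 4. School-level variation.** Give each school and period a random shift with SD s on the log rate. This adds 2s²/6 to the variance of the log rate ratio. It adds (D₁² + D₂²)s²/6 to the variance of the difference in shares, where D = m(1 + m/k)^(−k−1). For m = 1, k = 0.3 and a 15% fall:

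| s | Power, yes/no | Power, count |
|---|---|---|
| 0 | 61% | 93% |
| 0.1 | 42% | 58% |
| 0.2 | 22% | 26% |

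**The case against.** The strongest reply is that the cut is not shown to govern the main ODR analysis. Hypotheses about ODRs are tested in the mixed-model/GEE paragraph, where nothing makes the response binary, and Proc Genmod fits counts. The at-least-one variable carries only a yearly before/after interval. This stands: a reader might infer that the primary ODR comparison is blind to falls among repeat-referral students, and the article does not support that. On this view what remains is an unstated scale, which a condensed article may leave to the analysis plan. That part stands only for the model. The yearly analysis is a stated rule, and its variable does not match its own stated purpose.

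A second reply concerns size. A reader might infer that half or more of the information is lost. Without an ODR distribution that cannot be derived. It is true only above a mean of roughly 0.4 to 1.3 ODRs per student, depending on dispersion. The power figures also rest on independent students, although schools vary and many of the same students are measured at both times. With a school-by-period SD of 0.2 the two scales have nearly the same power. This stands as well.

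A third reply is that repeat-referral students are not the whole of Tier 2. Subcommittee referral is another route, and Tier 2 also takes anxious children, who need not have repeated ODRs. Tier 1 aims to prevent new cases, for which the share with any ODR is a relevant measure, and falls to zero do register. All of this is right. It is a reason to keep the prevalence as a description, but it does not make the prevalence a rate.

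**Conclusion.** The point holds in a limited form. As written, the yearly ODR analysis reports a prevalence where it promises a rate, and it is largely insensitive to falls among students with repeated ODRs unless they reach zero. In the illustration with mean 1 and k = 0.3, a 27% fall in total ODRs moves the share by about 0.9 percentage points.

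For a uniform 15% fall, the information lost is about 11–35% at means of 0.1–0.25 ODRs per student and 36–69% at means of 0.5–2. These ranges assume negative binomial counts with k from 0.2 to 0.6 and independent students. The power gap shrinks with school-level variation.

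Whether the loss reaches the between-condition test cannot be told from the article. If the model uses counts, the yearly analysis does not match it. If it uses the yes/no variable, the loss carries into the interaction test. Either way the two descriptions must be reconciled. The change is worth making because it is cheap and uses data already being collected.

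**What to change.** In the Data analytic plan, name one ODR response for both the mixed-model/GEE analysis and the yearly analysis: the number of ODRs per student, with enrolled school days as offset. Fit an overdispersed count model, such as a negative binomial with log link, in the Proc Genmod already named or in a mixed-model equivalent. Account for clustering by school with a small-sample correction, because robust standard errors from GEE are unreliable with only six clusters. Report the rate ratio with its 95% confidence interval. Keep the share of students with any ODR as a secondary description.

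The cost is a few lines of wording and one model in software already planned, on ODR data already collected. There are two small downsides: a rate ratio is slightly harder to read than a percentage of students, and a few very high counts need a robust or overdispersed model. The change does not remove the limits of having six schools, which apply on either scale.

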#### School climate

Perception of school climate will be assessed via a questionnaire [101] completed by 30 school staff per school (equal proportion of teachers, support staff and administrators) chosen at random in year one. The same school staff in each school will subsequently complete the survey at the end of each project year. The questionnaire has four factors: Skill Instruction; Support for Staff; Staff Respect for Students; and Safety. We will use all four factors in the analyses.

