In addressing aim three, school climate scores and the proportion of out-of school suspensions (number of suspension divided by number of students) served at the school during the previous academic year (*i.e.*, before implementation of Tier 1) will be compared to school climate scores (using the two independent sample t-test), and school suspensions for each subsequent project year (using Chi-squared test) respectively. For Tier 2, the proportion of children at baseline who are found to have unmet need for mental health services (*e.g.*, children found to have an externalizing or anxiety disorder at the intermediate or clinical level via the DISC-IV and who have not received mental health services as measured via the SACA) will be compared to the proportion of children with unmet need for mental health services in subsequent years (using Chi-squared test). In order to obtain a measure of unmet need at baseline, we will interview parents to assess the presence of disorders and service utilization at one year prior to the assessment and at the time of the assessment. For each subsequent cohort of children, we will interview parents about presence of disorder and service utilization only at the time of the assessment. Comparison of the proportion of unmet need between each subsequent year to the baseline proportion will be compared using Chi-square test.

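### Two of the tests named for aim three do not fit the data: an independent-samples t-test on largely the same staff, and a chi-squared test on suspension events per student

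*Protocol article*

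**What the plan says.** Aim three looks at change from year one to each later year, pooled over all six schools (Protocol article, Mental health disparities). For climate and suspensions, the Data analytic plan says the baseline values "will be compared to school climate scores (using the two independent sample t-test), and school suspensions for each subsequent project year (using Chi-squared test".

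- **Climate.** The School climate section has the questionnaire "completed by 30 school staff per school", sampled at random in year one, and adds: "The same school staff in each school will subsequently complete the survey at the end of each project year". The Data analytic plan completes the rule: "School personnel no longer present in the school during subsequent years will be replaced".
- **Suspensions.** The Data analytic plan defines the quantity as "the proportion of out-of school suspensions (number of suspension divided by number of students". The Children's functioning section lists two separate indices: suspensions per 100 students per year, and the "percentage of students receiving suspensions".
- **Unmet need.** At baseline, parents are asked about disorder and "service utilization at one year prior to the assessment and at the time of the assessment". Parents of later cohorts are asked "about presence of disorder and service utilization only at the time of the assessment". The proportions are compared by chi-squared test.

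Elsewhere the Data analytic plan gives mixed models and GEE as the general approach, and the Participants section says that information will be treated as nested within school. The aim-three paragraph carries neither through.

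**The concern.** An independent-samples t-test assumes that the two years' respondents are unrelated. Here they are mostly the same people, with some replacements, working in the same six schools. The standard error is therefore not the one the test computes.

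A chi-squared test on a 2×2 table assumes that each student falls once into a suspended or a not-suspended cell. Suspensions divided by students counts repeatable events: one student can contribute several, so the binomial variance does not apply. Many students also appear in both years.

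The unmet-need paragraph leaves open whether the one-year look-back enters the baseline proportion. Later cohorts have no matching measure.

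Aim three is where the trial would claim a change in disparities. As written, the precision attached to two of its comparisons is wrong, and the third is not fully defined.

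**Working it through.** The article states no power, effect size or alpha for aim three, so there is no figure to reproduce. The counts are consistent with Table 1: 30 × 6 = 180 staff and 650 × 6 = 3,900 students. Correlation, retention, suspension rate, dispersion and cohort size are not given. All values below for these are assumptions, at two-sided 0.05.

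**1. Climate, within-person correlation only.** Let n = 180 per wave, r = correlation between years, s = share of staff retained, SD = 1, true change 0.2.

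- SE the t-test uses: √(2/180) = 0.1054.
- True SE of the same difference: √(2(1 − s·r)/180).
- SE of an analysis that uses the pairing: √(2/(180s/(1 − r) + 180(1 − s))).

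| r = 0.5 | t-test SE | True SE | SE using pairing | Type I of t-test | Power, t-test | Power, using pairing |
|---|---|---|---|---|---|---|
| s = 1 | 0.1054 | 0.0745 | 0.0745 | 0.006 | 46% | 77% |
| s = 0.5 | 0.1054 | 0.0913 | 0.0861 | 0.024 | 47% | 64% |

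For s = 1, t-test power is Φ((0.2 − 1.96 × 0.1054)/0.0745) = Φ(−0.09) = 46%. Power using the pairing is Φ(0.2/0.0745 − 1.96) = Φ(0.72) = 77%. For s = 0.5, the figures are Φ(−0.07) = 47% and Φ(0.2/0.0861 − 1.96) = Φ(0.36) = 64%. A simulation at r = 0.5 with full retention gave a type I error of 0.005.

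**2. Climate, adding school-by-year variation.** Let x be the share of variance in shifts common to a school in a given year. With 30 staff in each school, r = 0.5 and full retention, the true variance of the difference is (2/180)(0.5 − x + 30x). It equals the t-test's 2/180 when 0.5 + 29x = 1, so x = 0.5/29 = 0.017. Above about 2%, the t-test's error bars are too narrow.

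**3. Suspensions.** Let the count per student be negative binomial with mean μ and dispersion k.

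- Variance assumed by chi-squared: μ(1 − μ).
- Actual variance: μ + μ²/k, multiplied by (1 − c) when the same students recur, where c = overlap × correlation.
- Type I error: 2[1 − Φ(1.96 √(assumed/actual))].

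| μ | k | Type I, c = 0 | Type I, c = 0.85 × 0.5 = 0.425 |
|---|---|---|---|
| 0.1 | 0.1 | 0.189 | 0.083 |
| 0.1 | 0.5 | 0.090 | 0.025 |
| 0.2 | 0.25 | 0.191 | 0.085 |
| 0.4 | 0.1 | 0.497 | 0.371 |
| 0.4 | 0.5 | 0.258 | 0.136 |

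Example for μ = 0.4, k = 0.1, c = 0: actual variance 0.4 + 0.16/0.1 = 2.0, assumed 0.24, ratio 8.33, type I 0.497. Over μ of 0.1, 0.2, 0.4 and k of 0.1, 0.25, 0.5, with and without overlap (18 settings), 16 exceed 0.05, one of them only just (0.051). The two below are at μ = 0.1 with overlap. A simulation at μ = 0.2, k = 0.25, c = 0 gave 0.18. These figures leave out school clustering.

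**4. Unmet need.** This is a matter of reading. The baseline interview yields a look-back measure and a current measure; later cohorts yield only the current one. The text does not say which baseline measure is compared.

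**The case against.** **The general approach already covers climate.** It names climate, and where the support-by-time interaction is not significant it reports the time effect over both support levels. That is nearly the aim-three question. But the aim-three paragraph names a different test, so the general statement does not cure it, and the plan could yield two p-values for much the same question.

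**The t-test is merely conservative.** This holds for within-person correlation alone. A reader might infer that the climate error bars are always too wide. The documents do not support that, because a school-by-year share of about 2% reverses the direction. The 46% against 77% contrast also assumes full retention, although the article provides for replacement and reports staff turnover in its pilot study.

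**The suspension error rates depend on assumptions.** This stands. A reader might infer that false positives are inflated in every case. With few suspensions and many recurring students the error can fall below 5%, and the article gives no suspension rate. A rate above one per student, which would make a cell of the table negative, is therefore only hypothetical. That the index is not a binomial proportion needs no such assumption.

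**School is dealt with elsewhere.** The Participants and Challenges and limitations sections do promise nested analysis. The fair criticism is that the aim-three paragraph does not apply it.

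**Conclusion.** The point holds for climate and suspensions: by the article's own description of the data, the named tests compute the wrong standard errors. For climate, the loss of power is about 30 percentage points with full retention (46% against 77%) and about 17 with half replaced (47% against 64%). Both figures assume r = 0.5, a 0.2 SD change and no school-by-year variation. For suspensions, the true type I error is about 2.5% to 50% under the assumed negative-binomial settings, mostly above 5%.

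Unmet need is a lesser point. A reader might infer that baseline and later cohorts are measured over different windows, so that any change would be partly an artefact. The text does not support this: the baseline interview also collects the time-of-assessment measure, nothing says that the look-back enters the compared proportion, and one year prior may mean a time point and not a longer window. What can be said is that the comparison is not fixed.

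Should-fix. Aim three is an uncontrolled before-after comparison. It is neither the randomised comparison nor the outcome on which the sample size was based.

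**What to change.** In the aim-three paragraph of the Data analytic plan:

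- **Climate.** Replace the t-test with the mixed model already planned: year as a fixed effect, staff and school as random effects. This uses retained and replacement staff together, which a plain paired t-test would not. A school intercept alone does not absorb school-by-year shifts, so state how these are handled.
- **Suspensions.** Analyse the percentage of students with at least one out-of-school suspension, or fit a negative-binomial model to the counts. Either way, model the students who recur across years; a plain chi-squared test on the percentage would still ignore them. Include school, for example as a fixed effect or with a small-sample correction, because standard cluster-robust errors are unreliable with six schools.
- **Unmet need.** State that the time-of-assessment measure is compared in every cohort, baseline included, and report the one-year look-back separately.

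The cost is wording and some programming. The percentage of students suspended is already to be recorded, so no new collection appears necessary, provided that suspension records can be linked by student across years.
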